## Abstract

**Background:**

Trauma is the most common cause of mortality among people between the ages of 1 and 45 years, costing Canadians 19.8 billion dollars a year (2004 data), yet half of all patients with major traumatic injuries do not receive evidence-based care, and significant regional variation in the quality of care across Canada exists. Accordingly, our goal is to lead a research project in which stakeholders themselves will adapt evidence-based trauma care knowledge tools to their own varied institutional contexts and cultures. We will do this by developing and assessing the combined impact of WikiTrauma, a free collaborative database of clinical decision support tools, and Wiki101, a training course teaching participants how to use WikiTrauma. WikiTrauma has the potential to ensure that all stakeholders (eg, patients, clinicians, and decision makers) can all contribute to, and benefit from, evidence-based clinical knowledge about trauma care that is tailored to their own needs and clinical setting.

**Objective:**

Our main objective will be to study the combined effect of WikiTrauma and Wiki101 on the quality of care in four trauma centers in Quebec.

**Methods:**

First, we will pilot-test the wiki with potential users to create a version ready to test in practice. A rapid, iterative prototyping process with 15 health professionals from nonparticipating centers will allow us to identify and resolve usability issues prior to finalizing the definitive version for the interrupted time series. Second, we will conduct an interrupted time series to measure the impact of our combined intervention on the quality of care in four trauma centers that will be selected—one level I, one level II, and two level III centers. Participants will be health care professionals working in the selected trauma centers. Also, five patient representatives will be recruited to participate in the creation of knowledge tools destined for their use (eg, handouts). All participants will be invited to complete the Wiki101 training and then use, and contribute to, WikiTrauma for 12 months. The primary outcome will be the change over time of a validated, composite, performance indicator score based on 15 process performance indicators found in the Quebec Trauma Registry.

**Results:**

This project was funded in November 2014 by the Canadian Medical Protective Association. We expect to start this trial in early 2015 and preliminary results should be available in June 2016. Two trauma centers have already agreed to participate and two more will be recruited in the next months.

**Conclusions:**

We expect that this study will add important and unique evidence about the effectiveness, safety, and cost savings of using collaborative platforms to adapt knowledge implementation tools across jurisdictions.

## Introduction

### The Research Question

#### What Is the Problem to Be Addressed?

Injuries represent a major health and economic burden for Canadians. They are the most common cause of mortality for people between the ages of 1 and 45 years [1], costing Canadians 19.8 billion dollars in 2004 in direct and indirect costs [2,3]. Up to half of all patients with major traumatic injuries do not receive evidence-based recommended care [4-8]. A recent study conducted in partnership with the Institut national d'excellence en santé et services sociaux (INESSS) and funded by the Canadian Health Services Research Foundation [5] determined that many trauma practices in Quebec’s trauma centers are substandard because they underuse proven therapies [4,5]. Studies in several other countries have identified adverse events, including death, that occur in trauma centers because of their failure to adopt best practices [9-13]. Aside from underusing proven therapies, there is also evidence of overuse of diagnostic procedures with known side effects, such as full-body computerized tomography (CT) scanning that exposes patients to unnecessary ionizing radiation that may increase the risk of cancer [14,15]. An estimated one million children every year in the US are unnecessarily imaged with CT [16].

Promoting best practices in trauma care has become an urgent and strategic investment for the health of Canadians and others [17,18]. Unfortunately, the implementation of best practices in the chaotic, acute trauma care environment is a difficult task because of three main factors, which are (1) macroenvironmental (eg, lack of financial resources), (2) organizational (eg, unclear definition of responsibilities within trauma team), and (3) professional (eg, resistance to clinical guidelines) [19]. Studying strategies used to implement best practices in trauma care, the Commonwealth Fund study [19] identified that trauma systems needed better knowledge management and coordination of care through well-implemented guidelines (ie, recommendations about what to do), protocols (ie, detailed procedures for how to administer care), and pathways (ie, frameworks for organizing who administers care and why). Moreover, these tools must be flexible and responsive to individual patients and to accumulating bodies of evidence. Many different health organizations have, therefore, started using wikis to manage knowledge and coordinate care [20-28]. Increasingly popular among health professionals [29-32], wikis are websites based on a novel technology that allow people to view and edit the website’s content, with viewing and editing privileges determined by different levels of access. Wikipedia—the best-known wiki—has 365 million visitors per month, is the sixth-most popular website in the world and its medical articles, available in 271 languages, are viewed about 150 million times per month [33].

In partnership with our team of researchers, the INESSS in Quebec is exploring how wikis could be used to improve the delivery of care to trauma patients. The INESSS oversees the quality of trauma care in the province of Quebec, Canada. It is also the accreditation body that designates different trauma center levels. This organization has expressed the need to explore wikis as a solution to improve the quality of care in trauma. To this end, we have conducted a scoping review that found that wikis could be effective in supporting the implementation of best practices in health care [34-39]. We also conducted a survey that identified that trauma professionals are willing to use wikis and that they share many positive beliefs about using them [40]. Specifically, wikis could serve as centralized knowledge management systems helping clinicians and decision makers coordinate the implementation of best practices by collaboratively building knowledge translation (KT) tools (eg, guidelines, protocols, pathways, and patient decision aids) that meet their needs [41-45] and monitor their use using novel Web metrics [46,47]. Wikis’ other interesting features included their low cost [40,48-51], their broad and global availability [33], their adaptability to local practices, and their capacity to empower stakeholders [52-54]. Wikis were perceived to facilitate the sharing and updating of KT tools by different professionals and to help clinicians working in rural areas where access to specialized care is limited [55,56].

Building on these results, we held a meeting funded by the Canadian Institutes of Health Research (CIHR) in May 2014 in partnership with the INESSS, the Trauma Association of Canada, and the Royal College of Physicians and Surgeons of Canada to plan a study to evaluate WikiTrauma (see Figure 1), a wiki we created to promote best practices in trauma care. At this planning meeting we decided to study its implementation in a limited number of Quebec trauma centers as a first trial for this novel intervention. We also decided to create Wiki101 (see Figure 2), a theory-based continuing professional development (CPD) program, that will train participants at the selected trauma centers to use WikiTrauma effectively and safely in order to create and share different types of KT tools (eg, care protocols, order sets, and patient decision aids).

Thus, in partnership with the INESSS and in collaboration with our other WikiTrauma partners, we propose an interrupted time series to measure the combined effect of Wiki101 and WikiTrauma on the quality of trauma care in four trauma centers in Quebec. We also propose to conduct a mixed-methods process evaluation in parallel with this trial to explore possible causal mechanisms about how our combined intervention succeeds—or fails—to lead to improved quality of trauma care.

**Figure 1 figure1:**
[figure not shown]
Screenshot of WikiTrauma order set.

**Figure 2 figure2:**
[figure not shown]
Screenshot of Wiki101 training program.

#### What Are the Principal Research Questions to Be Addressed?

Ultimately, we seek to test our hypothesis that our theory-based intervention (Wiki101) in combination with the use of WikiTrauma will result in better adoption of best practices in trauma care in Canada (see the conceptual framework in Figure 3), safer care (ie, fewer complications), improved patient outcomes, and less costly care.

**Figure 3 figure3:**

Conceptual framework underlying the proposed mechanism of action for the intervention.

#### Why Is This Project Needed Now?

Getting new evidence into health care practice is a slow and challenging process [57-65]. There is an ongoing and urgent need to find effective and low-cost methods of promoting best practices in all areas of health care [65-67] and, particularly, into interprofessional settings such as trauma care [17,68-72]. Recognizing that wikis capitalize on the free and open access to information, scientists, opinion leaders, and patient advocates have called for more research to determine whether wikis can equip decision-making constituencies to improve the delivery of health care [33,73], decrease its cost [49,74], and improve access to knowledge within developing countries [33,75-77]. Moreover, wikis are increasingly being used in health care by different academic institutions [32,41,78-81], health organizations [20,22,25,82,83], and health professionals [84-86] to share and disseminate information. As well, the principal knowledge user involved in our project (INESSS) is planning to use a wiki to promote best practices in trauma care, but would like to have more evidence about their use. Our CIHR-funded scoping review [34] confirmed that wikis have tremendous potential for improving the delivery of health care, but that a rigorous prospective trial to evaluate their effectiveness at implementing best practices is outstanding. Both our review and our survey identified an important need to test a theory-based approach addressing the main barriers that are preventing wikis from widely benefiting our health care system. The barriers most frequently mentioned, in order of frequency, were unfamiliarity with wikis, time constraints, lack of self-efficacy (ie, belief in one’s competence to use a wiki), and lack of access to a useful wiki containing reliable information for bedside decision making. For these reasons, we have designed WikiTrauma—a wiki promoting best practices—and Wiki101—a theory-based intervention—to maximize the potential benefits, to address the main barriers, and prevent any potential negative impacts of using a wiki to promote best practices in trauma care. In summary, there is sufficient evidence to support the conduct of this prospective interrupted time series for testing our novel intervention, which will combine a wiki to promote best practices in trauma care and a theory-based implementation strategy designed to maximize its benefit. This trial will inform our knowledge users about the impact of the combined effect of WikiTrauma and Wiki101 on the implementation of best practices in trauma care.

#### Best Practices in Trauma Care

##### Barriers to Implementing Best Practices in Trauma Care

Various aspects of trauma care can impede best practices [13]. Trauma professionals must often make quick decisions, mostly based on intuitive reasoning [87], which is fast, impulsive, effortless, and reflexive. While this serves trauma care well, it is also prone to error. Reminders (eg, care protocols) are knowledge tools [88] that improve intuitive decision making [87]. A recent systematic review indicated that noncomputerized reminders had the potential to improve practices in critical care [70]. Computerized reminders and clinical decision support systems, which were excluded from the previous review, offer different KT opportunities in trauma centers' hectic environments [89-91].

##### Systematic Reviews About Computerized Decision Support Systems and Barriers to Their Adoption

Systematic reviews indicate that computer-based reminders are effective interventions for fostering best practices in a variety of clinical areas [26,92-100], including in acute care [89]. Such reminders range from simple prescribing alerts to more sophisticated computer systems that support decision making. This said, health professionals have rejected many computer-based reminder systems on the grounds that they are slow, incompatible with work processes, unable to adapt to local practices, difficult to access, and/or are costly to implement [90,91,101-105]. Finding innovative ways to involve end users in designing, implementing, and evaluating reminder systems is key to increasing their use and their impact on health outcomes. Novel collaborative applications like wikis offer an easy and inexpensive solution [31].

##### Theoretical Framework Supporting the Use of Wikis as a Driver for Change in Health Systems

According to behavior-change theories, self-efficacy—roughly defined as an individual’s belief in his/her own competence—is one of the most important cognitive determinants of behavior [106-109]. By involving health professionals in sharing, updating, and creating practical reminders, wikis—highly accessible, interactive vehicles of communication—have the potential to increase professionals’ self-efficacy in using reminders [29,30,74].

##### Rising Use of Wikis in the Health Care System

Studies have found that 70% of junior physicians (mostly residents) use Wikipedia weekly [84], that 50-70% of physicians use it as a source of information in providing care [33], and that 35% of pharmacists refer to it for drug information [85]. Different large health care organizations (eg, Canadian Agency for Drugs and Technologies in Health [110-112], US National Institutes of Health [20,113], The Cochrane Collaboration [22], World Health Organization [83], and several universities [32,41,78-81,114]) are exploring the use of wikis and/or Wikipedia for different purposes. There is a rising use of wikis in health care and, consequently, increased potential safety risks involved with using nonvalidated information for the care of patients. Therefore, we believe there is an urgent need to evaluate the positive benefits wikis could provide in improving the quality of care, while limiting the potential negative effects. We intend to do this by conducting a rigorous and well-planned prospective trial in the controlled setting of a closed wiki (WikiTrauma) managed by strong central leadership (INESSS).

### Objectives

Our main objective will be to study the combined effect of WikiTrauma and Wiki101 on the quality of care in four trauma centers in Quebec using an interrupted time series design. Our secondary objectives will be (1) to evaluate the impact of our intervention on mortality, rate of complications, length of stay, and the Functional Independence Measure (FIM), (2) to evaluate participants' opinions about the combined intervention—Wiki101 and WikiTrauma, (3) to evaluate the quality of the different knowledge tools developed in WikiTrauma, and (4) to estimate the costs saved by sharing the different knowledge tools within WikiTrauma.

## Methods

### Pilot-Testing of WikiTrauma and Wiki101 Before the Prospective Trial

In consultation with two human factors specialists (HW, ST) and using the versions of WikiTrauma and Wiki101 developed at the planning meeting, we will further refine WikiTrauma and Wiki101 by employing user-centered design methods focused on our users' needs [115,116]. A rapid, iterative prototyping process with 15 health professionals from nonparticipating centers will allow us to efficiently identify and resolve usability issues prior to finalizing the definitive version of WikiTrauma and Wiki101 for the interrupted time series [117,118].

### What Is the Proposed Trial Design?

This study will be an interrupted time series with a parallel, theory-based process evaluation alongside the trial (see Figure 4). In the context of quality improvement, the interrupted time series is a simple but powerful tool used for evaluating the impact of a quality improvement program [119]. Our time series—repeated observations of the quality of care collected over time—will be divided into two segments. The first segment will comprise 10 retrospective, quarterly measurements of the quality of care measured before our intervention (a period of 30 months), and the second segment will be four prospective, quarterly quality of care measurements after our intervention (12 months). There are 57 adult-designated trauma centers of varying levels in Quebec—three level I, 26 level II, and 28 level III trauma centers. Four trauma centers will be selected in Université Laval's trauma network. We already identified one level I trauma center and a level II trauma center as participants. We will recruit two level III centers to complete our targeted sample of participating centers. Participants will not be blinded to their study assignment, however, all analyses will be blinded. The control group will comprise all of the 53 remaining adult trauma centers in the province.

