### What Are the Proposed Methods for Protecting Against Sources of Bias?

Although blinding of the participants and randomization are not feasible in this small trial, we will mobilize all efforts to minimize any other sources of bias. All data collectors (medical archivists) will be blinded to the allocation group. Throughout our study, we will prevent contamination by protecting Wiki101 and WikiTrauma by password and note any potential competing intervention. We will also identify any professional working in more than one participating trauma center to consider the impact of this potential source of bias. Wiki101 will be a standardized online training program. We will encourage all participants to complete all 12 months of the study. To minimize a potential Hawthorne effect, our control group will receive an invitation to consult the INESSS website at the beginning of the study. Moreover, our proposed study design of an interrupted time series provides the advantage of controlling for secular trends in the data.

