### How Will the Outcome Measures Be Measured at Follow-Up?

We will measure quarterly composite performance scores from the Quebec Trauma Registry for all 57 adult trauma centers. Data in the Quebec Trauma Registry is routinely collected in all Quebec trauma centers every 3 months. The composite performance score is calculated as the average of 15 other indicators routinely collected in the Quebec Trauma Registry [4]. This score has good discrimination, construct validity, criterion predictive validity, and forecasting properties [120]. Mortality rates, complication rates (for delirium, pneumonia, and deep venous thrombosis), length of stay, and FIM will also be measured on a quarterly basis for all 57 trauma centers from routinely collected data in the Quebec Trauma Registry. The intention to use WikiTrauma will be measured by a validated questionnaire [40]. The actual wiki use and the frequency of content modification will be measured on a quarterly basis using a Google Analytics account linked to WikiTrauma.

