### Data Analysis

Segmented regression will be used to measure, statistically, the changes in level and slope in the postintervention period compared to the preintervention period [119]. Thus, we will present a regression model with different intercept and slope coefficients for the pre- and postintervention time periods. We will compare the changes in quality of care measured at our four intervention trauma centers to the changes in quality of care measured at the other 53 trauma centers where no experimental intervention occurred. During the implementation period of WikiTrauma, we will continue to measure the impact on the quality of care. However, we will only proceed to compare the change in slope in the postintervention period once WikiTrauma has been fully implemented. We will use a Durbin-Watson test to verify the presence of autocorrelation and use an autoregressive error model to correct for this serial correlation.

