### Study Duration

This project is planned to last 18 months. We have planned 3 months to implement the trial, including ethics approval in the four designated trauma centers and for delivering Wiki101 to the four local trauma committees. We will analyze all retrospective data obtained from the Quebec Trauma Registry in the first 3 months of our study and every 3 months thereafter for a total of 12 months. The last 3 months will be used to prepare our datasets, conduct our various analyses, and write our final report.

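### The statement that all analyses are blinded cannot hold in a comparison of 4 with 53 centers, and archivist blinding is claimed without a mechanism

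*Protocol article*

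**What the plan says.** On analysts, the trial design section of the protocol article states: "Participants will not be blinded to their study assignment, however, all analyses will be blinded". On data collection, the section on protection against bias states: "All data collectors (medical archivists) will be blinded to the allocation group". That section also concedes that neither randomization nor participant blinding is feasible.

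The design section gives the group structure. On the total: "There are 57 adult-designated trauma centers of varying levels in Quebec". On the intervention side: "Four trauma centers will be selected in Université Laval's trauma network". On the control side: "The control group will comprise all of the 53 remaining adult trauma centers in the province". The Data Analysis section makes this the main contrast ("We will compare the changes in quality of care measured at our four intervention trauma centers to the changes in quality of care measured at", with the 53 control centers as the comparator).

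On where the outcome data arise, the section on outcome measurement says: "Data in the Quebec Trauma Registry is routinely collected in all Quebec trauma centers every 3 months". On timing, Study Duration says: "We will analyze all retrospective data obtained from the Quebec Trauma Registry in the first 3 months of our study and every 3 months thereafter", over 12 months in all. Data Analysis defers the comparison of post-intervention slopes until WikiTrauma is fully in place and gives no date or criterion for that.

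**The concern.** In an open, non-randomized study, masking of analysts and of outcome recorders is among the few protections left, and a reader will give credit for it. Here the masking of analyses is stated without limit, yet the design shows the analyst which group is which.

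This matters because a modeling decision is still open. The post-intervention segment starts at a point to be judged later, registry data are to be analyzed every 3 months meanwhile, and few post-intervention points are planned. Blinding would guard against a choice shaped by the results, and in the group comparison that guard is missing. The second worry is recording. If archivists at the four sites know that their hospital has the intervention, the process indicators there could be recorded more completely or more favorably without any change in care.

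**Working it through.** **Step 1. Group sizes.** Inputs from the trial design section: 3 level I, 26 level II and 28 level III centers; 4 intervention centers, namely 1 level I, 1 level II and 2 level III.

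- Total: 3 + 26 + 28 = 57, as stated.
- Controls: 57 − 4 = 53, as stated.
- Shares: 4/57 = 7.0% and 53/57 = 93.0%.
- Controls by level: 3 − 1 = 2, 26 − 1 = 25 and 28 − 2 = 26; these sum to 53.

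If the groups are labeled A and B, the one with four centers is the intervention group. The label hides nothing once the group variable is in the dataset.

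**Step 2. Who knows the allocation.** The design section says the level I and level II centers have already been identified. The Inclusion Criteria say the authors will identify the two level III centers. The study team therefore knows all four centers whatever coding is used.

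**Step 3. Outcomes without a control arm.** The Control Group section denies control participants any access to WikiTrauma. The Experimental Group section gives the pre-course, post-course and 12-month questionnaires to the experimental group. The outcome sections list visits, edits, self-reported use and intention to use WikiTrauma. These outcomes have data from 4 centers and none from 53, so no coding scheme can blind their analysis. A claim covering all analyses fails on this alone.

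**Step 4. What can still be masked.** Before the group variable is attached, the data are 57 coded center series. Cleaning, calculation of the composite and choice of the error structure can be done at that stage without knowing which four centers are treated.

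**Step 5. What is open while the groups are visible.**

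- The design section plans 12 months after the intervention in quarters: 12/3 = 4 points.
- Starting the segment one quarter later leaves 3 points, a loss of 1/4 = 25% of the post-intervention data. Two quarters later leaves 2 points.
- The Data Analysis section sets no rule for this start.
- The 30-month baseline (10 quarters) is already on record and is to be analyzed in the first 3 months of the study, so the model can be fixed on it.

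**Step 6. Archivists, with the sections set side by side.**

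- The bias section says they are blinded.
- The outcome measurement section places registry collection in the centers.
- The section on allocating participants describes presentations to the trauma committee, wide recruitment of clinicians and decision makers, and committee members teaching colleagues. The ethics section adds approval by the chief executive officer.
- Allocation is by center, so knowing that one's hospital uses WikiTrauma is the same as knowing its allocation.
- Against this, the individual-level Inclusion Criteria do not name archivists, access is by password, and no section says archivists are told of the study.

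These sections make archivist blinding doubtful. They do not show that it fails.

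**The case against.** The best defense is that the article is a condensed account. How masking is carried out is commonly left to the full protocol or analysis plan, and real masking is possible on coded center series. The design is openly disclosed as unrandomized, with unblinded participants, so nobody is misled about its basic nature. This stands in part: the absence of a masking procedure is no fault in an article, and some steps can be masked. But the article makes an unlimited claim. No later document can blind a comparison of 4 with 53 once the groups are attached, or an outcome that exists in one arm only.

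Two stronger readings are tempting, and the article does not support them.

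- A reader might infer that archivist blinding does not exist either. The article places collection in the hospitals but does not show that archivists learn the allocation. The baseline quarters also precede the intervention, so any unmasked recording would mainly touch the four post-intervention quarters.
- A reader might infer from Study Duration that four unmasked looks at the effect are planned. That section says registry data are analyzed every 3 months. It does not say that these runs compare the groups, and Data Analysis holds back the slope comparison until implementation is complete. The quarterly runs leave room for such looks but do not schedule them.

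**Conclusion.** The statement that all analyses are blinded is wrong as written and should be corrected. For the group comparison and the wiki-only outcomes, this follows from the article's own counts and outcome list and needs no outside assumption. Archivist blinding is an unsupported assertion: doubtful at 4 of 57 sites, not disproved, and without a stated means.

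No size can be put on the bias. The article gives no rate of differential recording, no standard deviation for the composite and no target effect in composite points, so any figure for inflated scores would be pure assumption. What can be sized is the room for choice: each quarter's delay in the segment start removes a quarter of the four planned post-intervention points. The harm through that choice depends on analysts seeing group results before the start is fixed, which the article does not plan but does not exclude. The point concerns a protection credited to the primary result. It does not show that the result will be biased.

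**What to change.** 1. **Limit the blinding claim.** Replace the sentence on analyses with text to this effect: *Data cleaning, calculation of the composite score and choice of the error structure will be done on coded center series before the group variable is attached. The comparison of intervention and control centers, and all analyses of wiki use and WikiTrauma questionnaires, will be unblinded.*
2. **Fix the model before opening post-intervention data.** Use the 30-month baseline to settle and date the model code: error structure, form of the control comparison and start of the post-intervention segment. The start should be a date or a criterion that does not depend on the outcome data, in place of a later judgment that WikiTrauma is fully in place.
3. **Restrict the 3-monthly runs.** State that they are data checks, and that the group comparison is run once, after the last planned quarter.
4. **Recast the archivist statement.** Keep it as an intention, namely that archivists are not told of the evaluation, and list possible unmasking at the four sites as a limitation.

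The cost is mainly protocol wording and earlier completion of model code. The study gives up a favorable blinding claim and has no effect estimates during the 12 months.
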